## Introduction

The Filipino aging population comprised about 7% of the country's total population in 2015 and is projected to increase by 11% in 2025 and 16% in 2045 (1). Like many other lower middle-income countries (LMIC), the Philippines is not only experiencing demographic aging but also undergoing epidemiological transition due to increased unhealthy diets, sedentary lifestyles, and poor healthcare leading to dramatic increase in dementia epidemic and its associated risks (2–4). In a population-based cohort study of Filipino older adults, aged ≥ 60 years, we found a dementia prevalence of 10.6% (5), much higher than the 7% estimate for Southeast Asia (2), and 23.2% had mild cognitive impairment (MCI). Almost half (48.1%) of those with baseline MCI status, from the same cohort, developed incident dementia after 3–4 years of follow-up (6) indicating MCI as a potentially progressive condition that makes older individuals at high risk for developing dementia (7). Progression from MCI to dementia occurs at a higher rate with an estimated conversion rate of 10–15% per year (7, 8). The odds of progressing to dementia is increased by 3.07 times among those with MCI (6) and further increased by 1.53–2.95 times higher if identified with comorbid conditions such as cardiovascular risks and metabolic syndrome (9). This condition is prevalent in Filipino older adults, with around 82.0% of men and 70.4% of women having at least one cardiovascular risk factor (hypertension, diabetes, dyslipidemia, and smoking) (5). Mixed pathologies and comorbidities are common in the MCI population; therefore, multicomponent treatment strategy is a reasonable approach (7, 10).

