### Sample Size Determination

Sample size was calculated based on the results of quasi-experimental study for INDAK where we compared the mean difference in ADAS-Cog, the primary outcome, from baseline and after 1-year follow-up between intervention and control groups. In that study, ADAS-Cog decreased by 3.16 (SD = 5.97) in the intervention group and 0.91 (SD = 8.69) in the control group (15), with an α error of 5% and β of 5% (power of 95%), and a one-tailed alternating hypothesis in favor of the intervention group, the sample size calculated is 136 per group or 272 for two groups (intervention and control). To account for clustering, a design effect of two will be adopted. This means that the total sample will be 544, with 272 participants per group. Allowing for 10% dropout, the final total sample size required in this study is 605 participants. This will be divided into 20–25 clusters per treatment arm. One cluster will have 12–15 participants, a range we found to be optimum for the intervention in the previous observational study. For MRI, at least 20% of the sample will undergo MRI, selected randomly from both intervention and control arm. This will be proportionally allocated to both arms. The estimated pilot size is 60 participants or 30 per group, expecting higher dropouts; 20% allowance was added giving a final pilot size of at least 72 or 36 per group. The pilot phase is to assess the acceptability of combined interventions (i.e., INDAK, vascular risk management, and nutrition counseling), determine adherence and dropout rates, as well as identify challenges and feasibility of conducting and advancing our research findings with neuroimaging outcomes.

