#### Improving Neurocognition Through Dance and Kinesthetics

Dance teachers are trained professional dance sport specialists with extensive experience in teaching ballroom dancing. INDAK consists of eight ballroom dances organized into 6-week modules with increasing complexity and intensity. The first week of each module introduces basic dance steps or figures then gradually progresses to more complex dance figures. The modules begin first with non-partnered dances allowing familiarization with one's own movement and followed later by dances with a partner, which is more complex and requiring interaction. The dance modules are Reggae, Cha-cha, Samba, Merengue, Bachata, Swing, Tango, and Salsa. The whole dance intervention lasts for 12 months. Each dance session is 60 min comprising of warm-up (5 min), dance proper (45 min), and cool down (10 min). Each session begins with review of previously learned dance figures, then integration of two to three new figures and then rehearsal of all learned dance figures with slow and fast music. The teacher shuffles the figures creating different sequences to test memory and cognitive ability. Concepts such as visualization, musicality exercise, improvisation, and dance recall are used. The nurse will use a logbook to register the frequency and duration of participation of each participant. From a previous study, adverse events were infrequent and limited to musculoskeletal pains in the first 2 weeks of the study (15). To ensure safety, a nurse will always be present at each session and liaise with local hospitals in case of unexpected adverse events. The nurse records vital signs (i.e., blood pressure and heart rate) of all participants before and after the dance. Compliance to INDAK intervention is defined as ≥80% attendance and completion of a full 60-min session for each attendance. Failure to participate or developing physical conditions that limits INDAK participation will be withdrawn from the study.

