#### Data Management and Statistical Analysis

Data will be encoded independently by two research associates, and inconsistencies will be double checked with the data source to ensure data accuracy. All tests (primary and secondary outcomes) will be analyzed as independent continuous measures; additionally, we will also analyze for executive function composite (EFC) score derived by dividing independent test scores with their maximum possible scores and summing across tests for EFC, as was done in previous studies (63–65).

The study will employ univariate, bivariate, and multivariate statistics. For univariate, descriptive statistics (mean/SD; frequencies/percentages) will be used to summarize sociodemographic and other baseline characteristics. The bivariate analyses that examine underlying relationships between the outcomes and other clinical characteristics are the following: independent *t*-test for continuous variables and Chi square test (or Fisher exact test when ≤ 20 of the cells have the expected count <5) for categorical variables to compare baseline data between the intervention and control groups. Pairwise comparison of the randomization groups per timepoint will also be done to explore differences at different times using independent *t*-test. For multivariate analyses, the study would estimate the effect from baseline to follow-up at 12 months between randomization groups. Since the participants will be assessed three times (at baseline, 6th and 12th months), the study will be using multilevel mixed models to test the significance between group means but controlling for possible confounders (i.e., when age, sex, and education were not successfully controlled for in the randomization design). Necessary diagnostics will also be considered. This multilevel model is appropriate as it can take into account the clustering effect, and the number of clusters in this study is moderately sized (25–30 clusters per arm).

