To analyze for the secondary outcomes, RM-ANOVA/RM-ANCOVA will also be used. Point estimates and their corresponding confidence intervals will be evaluated to assess precision and power. Very wide confidence intervals will signify underpowered analyses. Sensitivity analysis will be conducted including imputation of missing data using last observation carried forward or mean imputation. Data management will primarily be the responsibility of the research team. All data will be securely stored and accessible only to the researchers in compliance with the ethics approval of the study.

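### The missing-data sensitivity analyses named (last observation carried forward or mean imputation) do not vary the missing-at-random assumption, so they cannot show whether the result survives informative dropout

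*Protocol article*

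**What the plan says.** The main analysis is described in Data Management and Statistical Analysis. With assessments at baseline, month 6 and month 12, "the study will be using multilevel mixed models to test the significance between group means". The same section has the article's only sentence on missing data: "Sensitivity analysis will be conducted including imputation of missing data using last observation carried forward or mean imputation". It does not say which of the two methods will be used, or which mean (arm, overall or visit; score or change) will be imputed.

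Three other places bear on the point:

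- Sample Size Determination plans for dropout: "Allowing for 10% dropout, the final total sample size required in this study is 605 participants". For the pilot it adds a 20% allowance.
- The INDAK section under Multicomponent Intervention sets a withdrawal rule: "Failure to participate or developing physical conditions that limits INDAK participation will be withdrawn from the study".
- The Introduction describes a condition that tends to progress: "Progression from MCI to dementia occurs at a higher rate with an estimated conversion rate of 10–15% per year".

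**The concern.** A mixed model fitted by likelihood to all observed visits is valid if data are missing at random. A useful sensitivity analysis asks how far that assumption can fail before the conclusion changes. Neither named method asks this. Last observation carried forward (LOCF) puts one fixed assumption, no change since the last visit, in place of another. With visits six months apart, the score carried to month 12 is 6 or 12 months old. Mean imputation gives every dropout the average of those who stayed, treats that value as observed, and ignores the barangay clustering that the main model was chosen to handle.

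This matters more here because the withdrawal rule can remove people only from the arm that dances, and it does so for non-participation or physical limitation. Unequal, health-related loss is therefore foreseeable. The sensitivity analyses could then seem to confirm a result that dropout helped to produce, or cast doubt on a sound one.

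**Working it through.** **Inputs from the Protocol article.** Planning changes in ADAS-Cog, where lower is better: "ADAS-Cog decreased by 3.16 (SD = 5.97) in the intervention group and 0.91 (SD = 8.69) in the control group". The planned difference is -3.16 - (-0.91) = -2.25. The dropout step reproduces: 544/(1 - 0.10) = 604.4, rounded up to 605, so about 60 people are expected to be missing. The rest of the sample-size calculation plays no part here.

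**Assumptions, not in the document.** The split of dropout between arms, and the size of the change not seen in dropouts.

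**1. Does either method respond to what happened to the dropouts?** Let a fraction m drop out of the intervention arm only, let completers show the planned means, and let the dropouts' unseen change be D (positive is worse).

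- True difference = (1 - m)(-3.16) + mD + 0.91
- LOCF from baseline = (1 - m)(-3.16) + 0.91
- Mean imputation by arm = -2.25

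| m | D | True | LOCF | Mean imputation |
|---|---|---|---|---|
| 10% | 2 | -1.73 | -1.93 | -2.25 |
| 10% | 5 | -1.43 | -1.93 | -2.25 |
| 10% | 10 | -0.93 | -1.93 | -2.25 |
| 20% | 2 | -1.22 | -1.62 | -2.25 |
| 20% | 5 | -0.62 | -1.62 | -2.25 |
| 20% | 10 | +0.38 | -1.62 | -2.25 |

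D does not appear in the last two formulas. The truth can reverse sign while both answers stay where they are.

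**2. Direction of the LOCF bias**, at an assumed 15% (intervention) vs 5% (control) dropout.

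- No true effect, and everyone worsens by 2 to 5 points over 12 months. Carrying baseline gives a spurious benefit of (0.15 - 0.05) × 2 = 0.2 to (0.15 - 0.05) × 5 = 0.5 points. Carrying month 6, with linear worsening, gives half of that: 0.1 to 0.25.
- Planned improvement in both arms, with baseline carried: 0.85 × (-3.16) - 0.95 × (-0.91) = -2.686 + 0.8645 = -1.82. Against -2.25 this is a loss of 0.43, or 19%, toward no effect.
- Equal dropout and equal change in both arms: the bias is zero.

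**3. Mean imputation and the standard error (SE)**, for independent observations with a fraction m missing in each arm.

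*(a) The change score itself is imputed by its arm mean.* The naive variance is (1 - m)s²/n and the correct one is s²/[n(1 - m)], so the SE ratio is 1 - m.

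*(b) The month-12 visit mean is imputed and change is then analysed.* With equal SD s at both visits and correlation r, the naive variance is (s²/n)[(1 - m) + 1 - 2r(1 - m)]. The correct one is (s²/n)[1/(1 - m) + 1 - 2r]. The first is exactly (1 - m) times the second, so the SE ratio is √(1 - m) for any r.

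The true level of a nominal 5% test is 1 - Φ(1.645 × ratio) one-sided, or 2[1 - Φ(1.96 × ratio)] two-sided:

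| m | Case | SE ratio | One-sided | Two-sided |
|---|---|---|---|---|
| 10% | (b) | 0.95 | 5.9% | 6.3% |
| 10% | (a) | 0.90 | 6.9% | 7.8% |
| 20% | (b) | 0.89 | 7.1% | 8.0% |
| 20% | (a) | 0.80 | 9.4% | 11.7% |

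Simulation (20,000 runs) agreed. Case (a) gave 6.9% and 9.2% one-sided at 10% and 20% missing. Case (b) at 10% missing gave 5.8 to 6.0% one-sided and 5.9 to 6.4% two-sided.

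**The case against.** The strongest reply is that little hangs on this. The effect estimate, its interval and its test come from the mixed model, and the imputations only supplement it. The sentence says that sensitivity analysis will include these methods, so the list is open, and an analysis plan that is not shown may add better ones. All of this stands. A reader might infer that robustness will be judged by these two methods alone, or that the main result is compromised. The document supports neither. What can be faulted is that the protocol names two methods and both are poor.

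A reader might also infer that, because the condition progresses, LOCF must flatter the arm that loses more people. The document does not support a fixed direction. The annual rate it gives is for conversion to dementia, not for drift in ADAS-Cog, and in its planning study both arms improved. On those figures LOCF from baseline pulls the difference toward zero. It then denies dropouts any benefit, which is a real though crude departure from treating them like completers. It remains one fixed scenario, not a range.

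Finally, no single figure for mean imputation is justified. The quantity imputed is not stated, the sample-size hypothesis is one-tailed, and the 20% rate is the pilot's allowance, not the rate planned for the whole trial. The range is given for that reason.

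**Conclusion.** The point holds for the sensitivity analyses only. The two named methods are weaker than the model they would check, and neither responds to the outcomes of those who leave.

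- LOCF: under an assumed 15% vs 5% dropout, its error runs from a spurious benefit of 0.1 to 0.5 points (no true effect, assumed worsening of 2 to 5 points) to a dilution of the planned difference from -2.25 to -1.82. It vanishes when dropout and change are equal in the two arms.
- Mean imputation: at the planned 10% missing, the SE is about 5 to 10% too small. A nominal 5% test then runs at about 5.9 to 6.9% one-sided or 6.3 to 7.8% two-sided, and higher at 20% missing.

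The dropout splits and unseen changes are assumptions, and the SE figures assume independent observations. That neither method moves with the unseen outcome depends on none of these values.

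**What to change.** Keep the multilevel mixed model on all observed visits as the main analysis. Replace the sentence on LOCF and mean imputation with two steps:

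1. Multilevel multiple imputation with a barangay random effect, run separately by arm, using baseline and month-6 scores, age and education. Dance attendance can enter only the intervention arm's model, because it is logged only at dance sessions.
2. A delta-adjusted tipping-point analysis that worsens the imputed intervention-arm scores in steps until the conclusion changes, and reports that step. Worsening means higher scores for ADAS-Cog and lower scores for the Mnemonic Similarity Task and the executive function composite.

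The cost is a change of wording and some extra statistician time. No new data are needed. The article reports recruitment as stopped after eight clusters (72 participants), so the change can be made before most of the data exist.

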## Discussion

The FINOMAIN study will carry out the first multicomponent intervention in the Philippines for older adults with MCI. It will add to the limited evidence-based knowledge of complex interventions to reduce dementia risks in LMIC settings. The study aims to provide new scientific evidence to test an innovative model of community-based intervention program evaluating the effect of dance (INDAK) and managing for cardiovascular risks to maintain cognitive performance in a high-risk population. Its conceptualization is based on the rationale that risks for dementia are complex and multifactorial implying that no single approach is effective in addressing overall risks for cognitive decline (66). In this study, the multicomponent intervention is tailored fit to the local needs and cultural settings of the Filipino. Nutrition counseling and cardiovascular risk management are based on local guidelines. Dancing is an enriched way to introduce exercise as a leisure activity and at the same time provides enhanced social and cognitive stimulation (17). It is amenable to the social nature of the Filipino people who love to sing and dance. Furthermore, INDAK is portable, in that no special equipment or facilities are required to conduct it in the communities (15). In a low-resource setting such as the Philippines, this is a low-cost model of intervention that can easily be integrated in the existing services for older adults in the local communities.

This study was designed to target older populations with MCI. The INDAK modules are structured to input cognitively challenging tasks such as visualization, musicality exercise, improvisation, and dance recall as cognitive training elements with increasing intensity and complexity, apart from physical activity. These address limitations of other studies that used dance as intervention in older adults (67). Dance, when compared with repetitive and routine exercise, has superior positive long-term effects on hippocampal plasticity among healthy older adults (18–20). However, brain functional connectivity in response to dance, particularly among those with MCI, remains to be elucidated. Current studies revolving around dance are designed as single-component intervention and mostly explore therapeutic benefits on cognitive performance, and socioemotional and motor functions; however, this study will also explore potential neurological mechanisms of dance and cognition through brain MRI dance, which requires refined motor skills and integration of sensorimotor, proprioception, rhythm, and spatial awareness, which can facilitate cerebro-cerebellar integrity, the largest pathway in the brain. Exploring this connectivity can add understanding to cerebellar functions that explain benefits of dance on various cognitive domains.

## Study Status and Trial Registration

The study started recruitment and randomized eight clusters (72 participants). With the pandemic, the study was stopped and not actively recruiting. It is expected to resume when community restrictions will be eased by the local government. The study was registered with ClinicalTrials.gov on March 10, 2020. As the first participant for the pilot study was enrolled on May 28, 2019, this study was retrospectively registered (https://clinicaltrials.gov/ct2/show/NCT04301544).

## Ethics Statement

The studies involving human participants were reviewed and approved by St. Luke's Medical Center – Institutional Ethics Review Committee. The patients/participants provided their written informed consent to participate in this study.

